Once a participant’s results are reported, generally after 3 months, the results are sent to the genetic counselor. Results are reviewed and shared with the referring physician and/or a geneticist who then shares their interpretation about the significance of the genomic findings as well as their medical recommendations with the genetic counselor. An ad hoc discrepancy committee is available to review cases at the discretion of the genetic counselor for cases that have discrepant or unsatisfying results. The committee consists of NYCKidSeq medical geneticists, genetic counselors, laboratory directors, and referring providers. The decision of the discrepancy committee is used as a final diagnostic determination.

Each participant has a one-on-one result disclosure visit with a genetic counselor (ROR1). The referring physician can also participate in the appointment at their discretion. At the result disclosure appointment, the participant is informed of the results and their referring provider’s medical recommendations. The method of genetic counseling delivery depends on the study arm to which the participant is randomized. After genetic counseling, participants immediately complete the ROR1 survey with a study staff member. Six months after the ROR1 visit, approximately 9 months after study entry, a follow-up visit (ROR2) occurs either by phone or video. During this interaction, a study staff member administers the final survey (ROR2 survey).

Each subject’s genetic results may be reviewed every 12 months for the duration of the study. This is because information about genetic variants can change over time, as can the patient’s phenotype. As both types of information contribute to making a diagnosis, a re-analysis that recognizes reclassification of DNA sequence variants in a patient and their current phenotypic presentation can combine to change their original diagnosis. Variant reclassification information is derived by the laboratory from public databases such as ClinVar, while the refined phenotypic information is prompted by and entered into GenomeDiver following a review of electronic medical records. If results are reinterpreted, a new visit is arranged to inform the family of the finding. The visit to review the results is performed by a genetic counselor.

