### Study outcomes

#### RCT survey measures

The NYCKidSeq project is assessing participant outcomes through surveys administered at BL, prior to pre-test counseling and consent for the genomic testing, following the result disclosure genetic counseling during ROR1, and 6 months after disclosure of results at ROR2. The primary study outcome is the participant’s perceived understanding of genomic testing results, with comparison of results in SOC arm to GUÍA arm. The secondary study outcomes are objective understanding of genomic testing results and understanding of medical follow-up, the actionability of genomic results, and adherence to medical follow-up recommendations, with comparison of results in SOC arm to GUÍA arm. Additional participant outcomes focus on six domains: (a) attitudes toward genomic testing, (b) perceived utility, (c) psychological, (d) behavioral, (e) social, and (f) economic impact of genomic testing. With the exception of economic impact, all outcomes will be compared between the two study arms. The CSER consortium harmonized survey measures so that CSER projects, when possible, administer standardized survey measures [25] to facilitate combining data into a single data set for cross-consortium analysis. Table 2 summarizes participant outcomes being assessed across the three time points. When possible, previously validated measures were used. The BL and ROR1 surveys are administered in-person by a study staff member while the ROR2 survey is administered by a study staff member over the phone or video. Surveys are administered in either English or Spanish. All survey response data is entered and maintained in the REDCap database.

**Table 2 Tab2:** NYCKidSeq participant outcomes by survey timepoint

Variable	Source	BL^**1**^	ROR1^**2**^	ROR2^**3**^

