**Primary outcome**				
*Perceived understanding of genomic testing results*	NYCKidSeq developed measure (novel)	**–**	**X**	**X**

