#### RCT

Descriptive statistics will be calculated for quantitative survey instruments in the baseline, ROR1, and ROR2 surveys. In the case of missing data, when survey measures contain summary scores, a mean score will be calculated based on the responses provided. We will adjust for covariates, including age, sex, and race/ethnicity where appropriate. Repeated measures of analysis of variance (ANOVAs), chi-squared test, or regression models will be fit to the data in a simple paired design (*N* = 550 on each arm) to assess and identify significant improvements in parental understanding, satisfaction, and feelings about the results, and their subsequent behavior in the SOC group compared to the GUÍA group. A statistical significance criterion of *p* < 0.05 (after adjustment for multiple testing) will be used for all analyses.

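### If the first-named repeated-measures ANOVA is used for the primary outcome, families without the 6-month survey lose their observed ROR1 score, with loss of precision and possible bias

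*Protocol article*

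**What the plan says.** - **Outcome and timing.** Table 2 lists "Perceived understanding of genomic testing results" as the primary outcome, collected at ROR1 and ROR2 and not at baseline. The section on RCT survey measures defines its use "with comparison of results in SOC arm to GUÍA arm".
- **ROR1.** Under Procedures, Randomized controlled trial: "After genetic counseling, participants immediately complete the ROR1 survey with a study staff member".
- **ROR2.** Same section: "Six months after the ROR1 visit, approximately 9 months after study entry, a follow-up visit (ROR2) occurs either by phone or video".
- **Analysis.** Under Analysis of outcomes, RCT: "Repeated measures of analysis of variance (ANOVAs), chi-squared test, or regression models will be fit to the data". The same sentence describes the design as a simple paired one, with N = "550 on each arm", and covers understanding, satisfaction, feelings and behaviour together. It does not say which method belongs to which outcome.
- **Missing data.** Same paragraph: "In the case of missing data, when survey measures contain summary scores, a mean score will be calculated based on the responses provided". No other missing-data rule is given.

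**The concern.** With no baseline value, the only within-family pair for the primary outcome is ROR1 with ROR2. Classical repeated-measures ANOVA on two visits uses complete pairs. A family that answers at ROR1 and is not reached 6 months later would therefore leave the primary comparison, ROR1 score included. The stated missing-data rule works inside a survey that was at least partly answered; it cannot supply a score for a survey that was never taken.

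The discarded data are the ones least exposed to attrition after the intervention. ROR1 is completed with staff straight after counselling. Making its use depend on a remote contact half a year later adds a selection step after randomisation. The Discussion says the trial is unblinded, and the Study arms section gives only GUÍA families a personalised GUÍA report to take home. Retention that depends on understanding differently by arm is thus conceivable, though not documented.

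**Working it through.** **1. The plan's own figure.** 2 × 550 = 1100 randomised, and 1100 + 30 lead-in = 1130, as stated. The 550 cannot be derived further, because no effect size, SD, power or dropout rate is given. It equals the full randomised number per arm.

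**2. Precision.** Assumptions: every family has ROR1, one score with SD 1, 80% power, two-sided 0.05, no multiplicity adjustment. Detectable difference = (1.960 + 0.842) × √(1/n₁ + 1/n₂).
- All ROR1 scores, 550 and 550: 2.802 × √(2/550) = 0.169 SD.
- 20% dropped from each arm, 440 and 440: 2.802 × √(2/440) = 0.189 SD. This discards 0.20 × 1100 = 220 observed ROR1 scores.
- 20% and 30% dropped, 440 and 385: 2.802 × √(1/440 + 1/385) = 0.196 SD.

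**3. When bias arises.** The arm effect in the ANOVA is the difference between arms in the completers' mean of ROR1 and ROR2. Let ρ be the ROR1-ROR2 correlation (equal SDs), and let s be the completers' mean ROR1 minus the mean ROR1 of everyone in that arm. If dropout depends only on the ROR1 score, then

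bias = (1 + ρ)/2 × (s_GUÍA − s_SOC).

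With ρ = 0.5 the factor is 0.75. If dropout is unrelated to the score, both s are zero and there is no bias, whatever the loss rates. If it is score-related at the same rate and strength in both arms, the two s cancel. Bias needs a difference in rate or strength together with a relation to the score.

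Check of the formula, using the simulated case with 20% loss in each arm, score-related in SOC only, steep dropout: the ROR1 difference is 0.202 in all families and −0.045 in completers, so s_GUÍA − s_SOC = −0.247. Bias = 0.75 × (−0.247) = −0.185, and 0.202 − 0.185 = 0.017. The simulation gave 0.018.

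**4. Size under assumed inputs.** True effect 0.20 SD at both visits, ρ = 0.5, everyone has ROR1.

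| ROR2 loss, SOC / GUÍA | Relation to ROR1 score | Completer estimate (SD) |
|---|---|---|
| *Moderate dropout: log-odds −0.7 per SD* | | |
| 25% / 15% | none | 0.20 |
| 20% / 20% | low scorers lost, both arms alike | 0.20 |
| 25% / 15% | low scorers lost, both arms | 0.15 |
| 20% / 20% | low scorers lost, SOC only | 0.10 |
| 25% / 15% | low scorers lost, SOC only | 0.08 |
| *Steep dropout: probit slope −1 per SD* | | |
| 20% / 20% | low scorers lost, both arms alike | 0.199 |
| 20% / 10% | low scorers lost, both arms | 0.120 |
| 30% / 10% | low scorers lost, both arms | 0.044 |
| 20% / 20% | low scorers lost, SOC only | 0.018 |
| 20% / 20% | low scorers lost, GUÍA only | 0.386 |

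The direction is not fixed. With moderate dropout, 20% loss in each arm and low scorers lost in SOC only, the bias is −0.097 SD; by symmetry the GUÍA-only version gives 0.20 + 0.097 = 0.297.

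With 550 randomised per arm, the completer test rejects in 76%, 42% and 28% of trials in the three biased moderate scenarios (0.15, 0.10 and 0.08 SD). With no true effect, the 20% / 20% SOC-only scenario rejects in 40%.

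**5. Keeping all ROR1 scores.** A likelihood analysis of both visits that uses every ROR1 score gave 0.196 to 0.206 in the steep-dropout set, and about 0.20 in the moderate set. In these scenarios dropout depends only on the observed ROR1 score, which is the condition under which that analysis is valid.

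**The case against.** The strongest reply is that the article commits to nothing here. Repeated-measures ANOVA is one of three options joined by an or, for a whole family of outcomes, some of them measured once. Regression is also listed, and a between-arm regression at ROR1 or a mixed model would fit that word. A reader might infer that the plan drops every family without ROR2. The text does not support that; it follows only if the classical ANOVA is chosen. This stands, and the point is conditional for that reason. It does not remove the point, because the paired-design wording governs all three options and no mixed model is named.

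A reader might also infer that attrition differing between arms is enough to bias the effect. It is not: 25% against 15% loss unrelated to score returns 0.20. Nor is a difference in rates necessary, as the cases with equal loss show.

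The size of any bias is assumed throughout. The documents give no attrition rate, correlation or dropout mechanism, and the largest figures need score-related dropout in one arm only, which nothing in them establishes. The article also describes measures that favour retention: gift cards for completing all three visits, bilingual retention materials, stakeholder-board feedback on retention, and a remote ROR2. All of this stands and limits what can be claimed about magnitude.

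The 550 per arm may simply be 1100 divided by two. The article does not say that 550 families per arm will complete both surveys, so a claim that it assumes zero loss goes too far. The figure is still attached to a paired analysis, where it will be read as the number of pairs.

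Finally, a full protocol or SAP may settle the model. Lack of detail alone would be no criticism. The point is that the method named first, combined with the paired wording and a rule confined to answered items, is a poor fit to an outcome with one nearly loss-free visit and one remote visit.

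**Conclusion.** The point holds in conditional form. If the first-named classical ANOVA is used for the primary outcome, ROR1 scores from families without ROR2 are discarded. The certain cost is precision: with 20% loss per arm, 220 scores, and a detectable ROR1 difference of 0.189 instead of 0.169 SD. Bias is possible but not shown. It requires dropout related to understanding at a rate or strength that differs by arm. With a true effect of 0.20 SD, correlation 0.5 and 15-25% loss, the completer estimate lies between about 0.08 and 0.20 SD in the moderate-dropout scenarios tabulated. Steeper dropout widens the range, and score-related loss confined to GUÍA would push the estimate above 0.20. All of these rest on assumed attrition. The change is worth making because it needs no new data and removes an avoidable dependence of ROR1 on ROR2.

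**What to change.** In Analysis of outcomes, RCT:

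1. For the primary outcome, replace repeated-measures ANOVA with a likelihood-based linear mixed model with arm, visit and arm-by-visit terms, including every randomised family with a score at ROR1 or ROR2.
2. Report the arm difference at each visit from that model.
3. Describe 550 per arm as the number randomised, not as the number of analysed pairs.

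Cost: a change of wording and slightly more analysis work. The ROR2 estimate then relies on a missing-at-random assumption, so a sensitivity analysis for missing ROR2 scores is advisable. The model does not recover families lost between randomisation, which precedes the baseline visit, and ROR1.

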#### Diagnostic yield

We will also perform analysis to compare the clinical utility and diagnostic yield of WGS compared to TGP by comparing the results status (positive, negative, and uncertain) via each modality. We will focus our analysis on concordance, accuracy, and reproducibility as being most important for clinical utility. We will also examine differences in diagnostic yield of pathogenic, likely pathogenic, or uncertain variants across race/ethnicity groups.

## Discussion

The NYCKidSeq study aims to recruit 1130 children and their families, predominantly from Harlem and the Bronx areas of NYC to a RCT. Recruitment began on January 31, 2019, and is expected to be completed by May 31, 2021. Eligible children are suspected of having an undiagnosed genetic disorder in three disease categories: neurologic, cardiovascular, and immunologic. Two clinical genetic tests will be performed for each participant, either proband, duo or trio WGS (depending on sample availability) and proband TGPs. Clinical utility, cost, and diagnostic yield of both testing modalities will be assessed and compared. This study will evaluate the use of a novel, digital platform called GUÍA to digitize and standardize the return of genomic results and improve participant understanding, designed for both English- and Spanish-speaking families. The outcomes are parental understanding of and attitudes toward receiving genomic test results for their child, and behavioral, psychological, and social impact of genomic results. We will also conduct a pilot study to assess a digital tool called GenomeDiver designed to enhance communication between medical professionals and genetic testing labs, and evaluate its ability to increase diagnostic yield when used as a means to improve communication to share phenotypic and genotypic information, compared to standard practices.

There are several limitations to the study design, which includes the lack of blinding in the RCT. Participants and study staff are aware of participants’ randomization status as participants in the intervention arm are asked about their experiences using GUÍA specifically. In addition, GUÍA is unavailable in languages other than English and Spanish. After evaluating the use of GUÍA in these languages, we hope to expand the usability of GUÍA in other languages to be more reflective of the immense linguistic diversity of NYC.

In summary, the NYCKidSeq Study is investigating the effectiveness of integrating WGS into the clinical care of diverse and medically underserved children and their families in a variety of healthcare settings and disease specialties. This work is contributing to the broader NHGRI-funded CSER consortium, now in its second funding cycle. Goals of the consortium include assessing the clinical utility of WGS, exploring medical follow-up and patient outcomes, and providing new technology to enhance communication of genomic information within health systems and communities, and evaluating patient-provider-laboratory-level interactions that influence the use of this technology. The findings from this study, and the broader CSER consortium, will inform a clearer understanding of the opportunities and barriers of providing genomic medicine in diverse populations and clinical settings and contribute evidence toward developing best practices for the delivery of clinically useful and cost-effective genomic sequencing in diverse healthcare settings.

## Trial status

NYCKidSeq protocol version 10, October 15, 2019. Recruitment began on January 31, 2019, and is expected to be completed by May 31, 2021.

## Data Availability

De-identified data for this study will be shared in secure, access-restricted scientific research databases called The Database of Genes and Phenotypes (dbGAP) at the National Institutes of Health. Interpretations of the clinical significance of variants from genetic testing will be submitted to the ClinVar database at the National Institutes of Health.

## Abbreviations

TGP: Targeted gene panel
WGS: Whole-genome sequencing
GUÍA: Genomic Understanding, Information and Awareness application
SOC: Standard of care
ROR: Return of results
MS: Icahn School of Medicine at Mount Sinai
EM: Albert Einstein College of Medicine/Montefiore Medical Center
NYGC: New York Genome Center
